#### (c) Physical activities measurements

The OVC will be given an accelerometer to wear on the waist for seven consecutive days [35–37]. Although, the cut-off point for the moderate to vigorous physical activities for children varies in the literature [38, 39]. Smith et al., proposed moderate physical activity of 1535–3961 counts per minute and vigorous physical activity of ≥3962 counts per minute [40]. For the sake of this study, this model will be used [40]. The non-wearing period will be zero counts for ≥2 h and will be excluded from activities analysis [40–42].

#### (d) Academic performance

Academic performance will be obtained from standardised source via the participants’ school administrators or national academic records [43]. In this study, the most commonly reported assessed academic subjects (mathematics, reading, writing, life science) as reported in previous studies will be assessed [43]. The GPA of the selected subjects will be calculated with 80% as the cut-points for excellent academic performance.

#### (e) Nutrition knowledge, attitude, and practices of the caregivers

An interviewer-administered validated nutrition KAP questionnaire will be used for assessing the nutrition KAP of the caregivers of the OVC. The nutrition knowledge questionnaire has previously been used among adults in South Africa settings [44, 45]. The nutrition knowledge questionnaire has three sections. Section A consists of 60 questions with different subsections on nutrition knowledge [45] questions. Subsection A1 (17 questions) measures meal plan in which participants are required to choose an answer, while subsection A2 (7 questions) assesses food preparation with mostly true or false option questions. Subsection A3 (1 question) evaluates food purchasing knowledge of the caregivers and subsection A4 (35 questions) examines general nutrition knowledge.

Likewise the attitudes (Section B) and practices (Section C) questionnaires have been previously used among adults in India [46], as well as in a resource-limited setting of Kwazulu-Natal, South Africa [44]. Section B (8 questions) consists of questions on nutrition attitudes. All the questions have three options: Agree (1), disagree (2) and don’t know (3). Section C has three subsections: subsection C1, nutrition practice using FAO food groups. Participants will be asked questions on how often the nine food groups were eaten in the previous week. Information on the caregivers’ smoking and alcohol habits will also be obtained with questions from subsection C2 (two questions on smoking habits) and subsection C3 (2 questions on alcohol use).

### Planning and development of the nutrition education programme

The needs of the OVC will be identified in the results of Phase 1. The results also will guide the contents of the NEP in Phase 2. The aim of Phase 2 will be to develop an NEP tailored to the needs of OVC using the results from Phase 1, as well as existing guidelines and information from the literature.

The development process will be guided by the steps for designing a theory based NEP [47, 48]. The steps as described by Sahyoun et al., [48] and Contento, [47, 49, 50] will be contextualied, which include:Identification of needs and problems analysis.Stating the goals and objectives of the NEP.Identification of barriers to healthy behavior.Identification, selection, and contextualization of behavior/learning theories.Programme components selection and identification of the key educational goals.Preparation for the implementation of the NEP.Pre-testing of the nutrition education materials.Process and outcome evaluations.

### Intervention

The intervention will entail the implementation of the NEP at the orphanage homes. Selected constructs of the SCT and HBM will be incorporated to enhance learning, and positive changes in attitudes and dietary behavior to improve QoL, dietary diversity, physical activities, anthropometric status and academic performance of the OVC. The NEP will address the importance of nutrition in improving QoL and the secondary outcomes, and provide guidance on how to overcome the barriers to healthy eating to enable the caregivers of the intervention group to adopt typical behaviors [49, 51].

The intervention participants will receive nutrition education materials and the 12-week NEP. The NEP is proposed to consist of:(i)a NE trainer’s manual(ii)a participant’s workbook to be used at home by the intervention participants to revise the topics that will be taught. This proposal is expected to enhance participants’ confidence in performing acquired knowledge and skills [49, 51].(iii)flipcharts for pictorial demonstration; so that participants will compile evidence through visual literacy.(iv)a leaflet summarising the NEP for self-learning.

An attendance register will be kept for follow up and measure of attrition rates.

### Data procedures

Before the needs’ assessment data collection, a series of training sessions will be held to train the research assistant responsible for taking measurements, including QoL, dietary intake assessments, body composition, and anthropometric measurements, physical activities and nutrition KAP of the caregivers. The training will be for three weeks, to be held at the South African Research Chair: Education and Care in Childhood, Faculty of Education University of Johannesburg project office. To ensure standardisation and quality of data collection, this training will include an overview of all the measurement procedures in the protocol, and demonstration of the measurement techniques. The questionnaires will be subjected to face validity, such as clarity, simplicity, and readability of the content of the questions. This process will be conducted by the principal investigators [52, 53]. The questionnaires will be pretested following the procedure described above among at least 50 conveniently sampled OVC and ten caregivers. The reliability test will be done (using Cronbach alpha) to measure the internal consistency of the questionnaires. Anthropometric data will be collected individually using the school clinic. The dial indicator of the BCA will be checked regularly and adjusted to the appropriate zero reading position before use. A non-stretchable tape measure will be used in measuring the MUAC. To ensure reliability, measurements will be done two times for each participant [54].

### Data management and analysis

The quantitative data will be entered into EXCEL (version 15; 2016), and data will be cross-checked by re-entering the data on a separate spreadsheet for comparison. Double data entry will be done to ensure the quality of the data. Data will be analyed using the Release 10, 2007 of Stata Statistical Software and SPSS packages. Data will be subjected to a normality test (Shapiro-Wilk test). The means, standard deviations (SD) and medians (interquartile range) of the continuous data will be calculated. The frequency and percentage distributions of categorical data will be described. The reliability test (Cronbach alpha) will be done to measure the internal consistency of the questionnaires.

The nutrition knowledge scores of participants will be calculated based on a possible maximum of 60. Each subsection ‘s score of the nutrition knowledge questionnaire will be calculated and converted to percentages. The mean percentage of knowledge scores will also be calculated. Whati et al., performance rating scale of < 34% - very poor; (ii) 34 to 51% - fair/below average; (iii) 52 to 57% - good/average; (iv) 58 to 75% - very good/above average; and (v) 76 and above – excellent [45, 55] will be used to classify the nutrition knowledge performance.

Nutrition attitudes have eight dichotomous (agree, disagree) responses questions and the score will be the percentage of the total possible score (affirmative responses) using 60% as the cut-off for poor attitude performance [44].

The dietary practices will be classified based on how often participants consumed the FAO nine food groups [31] in the previous week. Participant’s lifestyle will also be classified based on the number of drinks containing alcohol and cigarettes consumption per day.

The construct of the QoL, nutrition knowledge and IDDS will be summarised by sex and age using percentages and 95% confidence intervals. Analysis of variance will be used to compare the intervention and control groups, to confirm the similarity in participant populations.

Multivariate regression analysis will be used for group comparison of overall QoL and the QoL constructs of the intervention and control groups. Other measurable outcomes will be compared (the baseline, week 12 and week 24) using baseline data as covariates. All the testing will be done at the 0.05 level of significance.

Atlas ti.8 software will be used for the qualitative data analysis. Focus group discussion will be recorded and transcribed verbatim by an independent person. To eliminate bias, the transcription will be coded by two independent researchers. Inconsistencies will be discussed until an agreement is reached.

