**Methods:**

A longitudinal study, and a mixed-methods approach steered by action research will be used. This study will be in three phases. Phase 1 will be the needs assessment; Phase 2 will be the development of nutritional education materials, and Phase 3 is the intervention. QoL, dietary intakes, body composition, and anthropometric status, physical activities, and AP of 520 OVC in Soweto will be assessed using standard techniques. Nutrition knowledge, attitude and practices (KAP) of the caregivers will be assessed using previously validated questionnaires. Focus group discussion (FGD) will be conducted to gain an in-depth understanding of what OVC eat and factors affecting their food intakes. Data will be collected at baseline, week 12 and week 24. Generalised Least Squares (GLS) regression model will be used to test the study hypotheses. Atlas-ti and Thematic Framework Analysis (TFA) will be used for qualitative data analysis.

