### Sample size

The sample size in this study was estimated based on the expected number of consenting participants in the two groups (control and the intervention group). This study desired 80% power (Z_β_ = 0.84) to estimate sample size with confidence interval (Z_∝/2_ = 1.96) of 95% as used in previous studies [16]. The investigator desires to detect a difference (d) of 5 points on a 100 point scale of QoL constructs between pre and post intervention [16, 17]. Standard deviation (*σ*) of 10 is expected in the QoL constructs between pre and post intervention [17]. Sample size (n) of 63 OVC per group (control and the intervention) to make a total of 126 OVC using the formular below is projected [18, 19].

*n* = 2(*σ*)2(*Z*_*β*_ + *Z∝*/2)2 ÷ *d*2

In order to compensate for non-response and drop out, 100% will be added to make a sample size of 126 anticipated consenting participants per group to make a total of 252 participants [18]. For the need’s assessment (Phase 1) a total of 252 is appropriate but 520 is proposed in order to further compensate for non-response and drop out.

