### Primary outcome

QoL will be measured using Kidscreen health-related QoL questionnaire for children and adolescents. This questionnaire has previously been validated in South Africa and shows acceptable psychometrics reliability of 0.76–0.81 [20].

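### The abstract tests the study hypotheses with GLS regression, but the analysis section never mentions GLS and gives the primary QoL comparison to multivariate regression; the two need not agree if loss differs by arm

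*Protocol article*

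**What the plan says.** - **Abstract, Methods:** "Generalised Least Squares (GLS) regression model will be used to test the study hypotheses". The same paragraph gives the schedule: "Data will be collected at baseline, week 12 and week 24".
- **Primary outcome:** "QoL will be measured using Kidscreen health-related QoL questionnaire for children and adolescents".
- **Data management and analysis**, the only section on quantitative analysis: "Multivariate regression analysis will be used for group comparison of overall QoL and the QoL constructs of the intervention and control groups". The next sentence turns to the remaining outcomes: "Other measurable outcomes will be compared (the baseline, week 12 and week 24) using baseline data as covariates". Visits and baseline covariates are mentioned there and not in the QoL sentence. The section ends with "All the testing will be done at the 0.05 level of significance".
- **Sample size:** "This study desired 80% power" for a 5-point difference with SD 10, giving 63 per group. Then: "In order to compensate for non-response and drop out, 100% will be added to make a sample size of 126" per group.

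GLS appears in the abstract and nowhere in the body of the article.

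**The concern.** The article names a model for the main hypothesis in two places, and the names differ. This is a conflict in the published text, so it is not a detail left to an analysis plan that is not shown. A later plan could follow either statement and claim to match the protocol, which leaves room to choose after the data are seen.

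The choice can affect the result. A GLS model fitted over the follow-up visits can use the week-12 value of a child who has no week-24 value. A regression run on children with complete data at week 24 cannot. Only the intervention group receives the 12-week programme, the design is quasi-experimental and recruitment is by convenience, so reasons for leaving could differ between the arms. The size of the drop-out allowance shows that the authors expect that loss may be large.

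**Working it through.** **1. The plan's own figures.** With d = 5, SD = 10, z = 0.84 and 1.96:

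n = 2 × 10² × (0.84 + 1.96)² / 5² = 200 × 7.84 / 25 = 62.72, so 63 per group.

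Adding 100% gives 126. The loss this tolerates is 1 − 63/126 = 50% of those enrolled. Power is 80.1% with 63 per group and 97.8% with 126. The plan's figures reproduce and nothing here changes them.

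**2. The two statements side by side.**

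| | Abstract | Data management and analysis |
|---|---|---|
| Model | GLS regression | Multivariate regression |
| Applied to | The study hypotheses | Overall QoL and the QoL constructs |
| Visits for QoL | Three data collections for the study as a whole | None stated |
| Baseline QoL as covariate | Not stated | Not stated (only for other outcomes) |
| Within-child correlation | Not stated | Not stated |

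**3. Can the choice matter?** Simulation, 126 per group, SD 10 at each visit, equal correlation between visits, all children seen at week 12, some lost before week 24. Only n and SD come from the document; the correlation and loss mechanism are assumed.

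- *Complete-case:* regress week-24 QoL on group and baseline QoL among children seen at week 24; the estimate is the group coefficient.
- *Using week 12:* (a) regress week-12 QoL on group and baseline in all children, group coefficient b1; (b) regress week-24 QoL on group, baseline and week-12 QoL in those seen at week 24, group coefficient b2 and week-12 coefficient e. The estimate is b2 + e × b1. With this loss pattern it is equivalent to a likelihood-based GLS fit over the two follow-up visits with baseline as covariate.

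No true effect. Loss in the intervention arm is more likely at low week-12 QoL and control loss is random, except in the last row:

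| Loss before week 24 | Log-odds per SD | Correlation | Complete-case | Using week 12 |
|---|---|---|---|---|
| 50% | 1 | 0.5 | 1.0 to 1.1 | 0.0 |
| 50% | 1 | 0.7 | 0.9 | 0.0 |
| 30% | 1 | 0.5 | 0.6 | 0.0 |
| 20% | 1 | 0.5 | 0.5 | 0.0 |
| 10% | 1 | 0.5 | 0.2 | 0.0 |
| 20% | 0.5 | 0.5 | 0.2 to 0.3 | 0.0 |
| 50%, same dependence in both arms | 1 | 0.5 | 0.0 | 0.0 |

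Ranges are results from separate runs. At 50% loss and correlation 0.5 the SD of the estimate across runs is about 1.5, so a 1-point bias is about two-thirds of it.

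True effect of 5, about half lost:

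| Loss pattern | Correlation | Complete-case | Using week 12 |
|---|---|---|---|
| None or random | 0.3, 0.5, 0.7 | 5.0 | 5.0 |
| Intervention arm depends on week-12 QoL, log-odds 1.5 per SD | 0.3 / 0.5 / 0.7 | 6.1 / 6.4 / 6.2 | 5.0 / 5.0 / 5.0 |

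With this steeper dependence the bias is about 1.1 to 1.4 points.

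**4. What baseline adjustment adds.** The groups are not said to be randomised. Take a stable baseline difference of 2.5 points (assumed), no effect, and correlation 0.5. A model without baseline QoL reports about 2.5 points. A baseline-adjusted one reports about 2.5 × (1 − 0.5) = 1.25. Leaving baseline out could therefore do more harm than the attrition bias above, and adjustment removes only part of the imbalance.

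**The case against.** GLS is an estimation method, and a multivariate regression with correlated outcomes can itself be estimated by GLS, so the abstract might name the estimator and the Methods the model. That is possible, and it is why the two should not be called proven rivals. But the QoL sentence gives no visits, covariates or correlation structure by which a reader could recognise the same model under another name, so the need to reconcile them stands.

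Three stronger readings are tempting, and the document supports none of them.

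- *That the abstract fixes a repeated-measures model.* It says only GLS regression; the repeated-measures form is inferred from the three data collections.
- *That the Methods version discards every child who withdraws.* The section is silent on incomplete data. Fitted visit by visit, it would still use such a child at week 12. Complete-case use at week 24 is one way to carry it out, and handling of missing data is commonly left to the analysis plan.
- *That half the children are expected to be lost after week 12.* The 100% allowance covers non-response and drop-out together, and a non-responder may never have a week-12 value. Fifty per cent is an upper bound on the late loss allowed for.

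It is also fair to object that the simulation compares single-outcome regressions, not a multivariate regression of overall QoL and constructs, and that its largest figures need heavy late loss with dependence in one arm only. Both objections stand. The simulation shows that the choice can matter; it does not predict how much it will.

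**Conclusion.** The inconsistency is real: the abstract and the analysis section name different models for testing the primary outcome, and nothing in the article reconciles them. It should be corrected.

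The effect on the result is conditional. It arises if the Methods version is run as a complete-case regression at week 24 and late loss depends on QoL differently in the two arms. In the severe case of 50% late loss, dependent in one arm only, the bias is about 1 point at log-odds of 1 per SD, or 20% of the 5-point target, and up to 1.4 points with the steeper dependence tried. It is about 0.2 to 0.6 points at 10 to 30% loss, and nil when loss is random or depends equally on QoL in both arms. GLS is protected only if loss depends on observed values alone. A reader might infer that the Methods analysis is biased whenever loss is related to week-12 QoL; the equal-dependence run shows that this is not so.

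**What to change.** Make the analysis section agree with the abstract by naming one primary model: a GLS (or mixed) repeated-measures regression of QoL at weeks 12 and 24 on group, visit, group-by-visit and baseline QoL, including every child with any follow-up QoL value. Apply it to overall QoL and, in the same form, to each QoL construct, since the sample size is based on the constructs. Keep multivariate regression only as a supportive analysis. Baseline QoL belongs in the model because the groups are formed without stated randomisation.

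The cost is wording and slightly more analysis work. No sample-size figure changes and no extra data are needed.

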## Methods

### Design

This longitudinal study will be in three phases. The study phases will be conducted consecutively because the phases will be mutually dependent. Phase one will be exploratory descriptive using a mixed method research approach in the qualitative and quantitative research domains. The first phase will provide information that will guide Phase 2 and Phase 3. Phase 2 will be the development of nutrition education materials based on the outcome of phase one. The third phase is an intervention in a quasi-experimental domain.

The overview of the study is illustrated in Figs. 1 and 2.

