### Settings and sampling

The study sites will be in selected schools in Soweto as stated in the broader study of the research chair in the application submitted to the Department of Science and Technology, National Research Foundation and the Faculty of Education Research Ethics Committee of the University of Johannesburg. Convenience sampling will be used to recruit the participants for Phase 1 and 3 of the study. Convenience sampling means to recruit participants who are willing and ready to give their oral and written consents during the data collection.

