***Food intakes using 24-h recall***

A single day non-quantified 24-h recall of OVC will be obtained from the participants via their caregivers/families. The recall will cover all days in a week. The individual dietary diversity score (IDDS) of the OVC will be used to measure the nutritional quality of the reported intake of the OVC [30–32]. The IDDS is a simple count of food groups that an individual has consumed over the previous 24 h. When the participants’ recall is complete, the foods will be classified according to the Food and Agriculture Organization of the United Nations (FAO) food groups and scored on a scale of Yes (1) or No (0) [31]. If a food item from the group is consumed, it will score ‘1’ and if not it will score ‘0’. The nine food groups will be (i) cereals, roots and tubers (ii) dark green leafy vegetables (iii) other vitamin A rich fruits and vegetables (iv) other fruits and vegetables (v) legumes and nuts (vi) meat and fish products (vii) organ meat (viii) milk and milk products (ix) eggs. The IDDS is sensitive to assessing the change in diet before and after an intervention to detect any improvement [31].

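### In a non-randomised comparison, adjusting for a one-day baseline diet score can leave part of a true group difference in the programme estimate

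*Protocol article*

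**What the plan says.** The Design section of the protocol article states: "The third phase is an intervention in a quasi-experimental domain". Settings and sampling adds: "Convenience sampling will be used to recruit the participants for Phase 1 and 3 of the study". No random allocation to programme or control is described.

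For the secondary outcomes, Data management and analysis states: "Other measurable outcomes will be compared (the baseline, week 12 and week 24) using baseline data as covariates". The same section plans an analysis of variance to confirm that the two groups are similar. The Abstract says that a generalised least squares (GLS) regression model will test the hypotheses, without giving its form.

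Diet is measured as follows: "A single day non-quantified 24-h recall of OVC will be obtained from the participants via their caregivers/families". It is scored by food group: "The IDDS is a simple count of food groups that an individual has consumed over the previous 24 h". No repeat of the recall at the same visit is described, and no reliability is given for the IDDS.

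The only reliability range stated is for the quality-of-life questionnaire, under Primary outcome: it "shows acceptable psychometrics reliability of 0.76–0.81". In text dealing with anthropometry, Data procedures says: "To ensure reliability, measurements will be done two times for each participant".

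**The concern.** With randomised groups, a noisy baseline covariate costs precision but causes no bias, because no systematic baseline difference has to be removed. Here the groups are formed without randomisation, so a real difference in usual diet before the programme is possible. Adjustment then has to remove that difference. A regression on an error-prone baseline has a flattened slope, so it under-corrects.

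A one-day count of food groups is a plausible case of substantial error: a child's score depends on the day recalled and on what the caregiver reports. If the programme group started with better diets, part of that head start could be reported as impact. If it started worse, a real benefit could be hidden. A larger sample does not help: the bias stays the same while the standard error shrinks. Evaluating impact is the study's third objective, so the estimate matters.

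**Working it through.** **Plan's own figure.** The Sample size section uses d = 5, SD = 10, Z = 0.84 and 1.96: n = 2 × 10² × (0.84 + 1.96)² ÷ 5² = 62.7, so 63 per group. Doubling for non-response and dropout gives 126 per group. Both reproduce. They bracket the number analysed if losses stay within the allowance.

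**Inputs not in the documents (assumed).** True baseline gap g = 0, 0.25 or 0.5 within-group SD. Reliability λ = 0.3–0.5 for a one-day IDDS and 0.95 for a precise measure. The gap is stable over time, errors are independent between visits, and the programme has no effect.

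**Bias.** With observed SD set to 1, the within-group slope of follow-up on observed baseline is λ. The adjusted group estimate is therefore g − λg = (1 − λ) × g.

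**Error rate.** The residual variance is 1 − λ². The variance of the adjusted estimate is about (2/n) × (1 − λ²) × (1 + g²/4). For g = 0.5, λ = 0.5, n = 126:

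- bias = 0.5 × 0.5 = 0.25
- SE = √[(2/126) × 0.75 × 1.0625] = 0.112
- ratio = 2.22, so P(significant) ≈ Φ(2.22 − 1.96) ≈ 0.60

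Simulation of the covariate model (4,000 runs per case, two-sided 5%) agrees:

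| Gap (SD) | λ | Spurious effect (SD) | Significant, 63 per group | Significant, 126 per group |
|---|---|---|---|---|
| 0 | 0.3–0.95 | 0 | about 5% | about 5% |
| 0.25 | 0.5 | 0.125 | 13% | 20% |
| 0.25 | 0.3 | 0.175 | 18% | 29% |
| 0.5 | 0.5 | 0.25 | 35% | 60% |
| 0.5 | 0.3 | 0.35 | 51% | 80% |
| 0.5 | 0.95 | 0.025 | 8% | 9.5% |

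For illustration only, λ = 0.76–0.81 with a 0.5 SD gap leaves 0.12–0.10 SD, and gives 18–15% with 63 per group and 29–24% with 126.

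**Does the planned ANOVA protect?** In the same simulations, a true 0.25 SD gap was significant at baseline in about 29% of studies with 63 per group and 51% with 126. A non-significant result would not show that the groups are alike, and the test removes no gap.

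**If errors persist.** If half the error variance recurs at each visit, the slope rises to λ + (1 − λ)/2, and the bias halves to (1 − λ)/2 × g. At g = 0.5 this is 0.125 SD (λ = 0.5) to 0.175 SD (λ = 0.3).

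**Change from baseline.** In the cases tabulated it rejected in about 5%. That follows from assuming a stable gap. If membership had depended on the observed baseline itself, the covariate model holds 5%. The change comparison then rejects falsely in about 25%, 55% and 68% of studies at λ = 0.8, 0.5 and 0.3 (gap about 0.5 SD, 126 per group).

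**The case against.** Baseline-covariate adjustment is a standard method, and a second analysis is the kind of detail that a condensed article may leave to a fuller plan. This stands in part: the adjustment itself is not an error and should be kept. But it is a choice the article states, for a design the article states, so its limits can fairly be raised.

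The text is also open to a wider reading. It speaks of baseline data, lists baseline among the compared visits, and the Abstract names a GLS model. Such a model could hold a contrast with baseline as an outcome. This also stands: a reader might infer that the plan fixes a single-covariate model as its only analysis, and the wording does not go that far. Equally, no passage specifies the other model.

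A reader might infer that every secondary outcome, or quality of life, is distorted. The documents do not support that. The quoted sentence concerns the other outcomes, so the questionnaire's reliability is illustrative only. Anthropometric measurements are described as duplicated, accelerometers are worn for seven days, and marks come from school or national records. For precise measures little of a gap would remain.

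Lastly, a reader might take the change analysis as the correct replacement. It is not: the way children enter each group is not described, and the ranking of the two methods reverses if entry depended on the observed baseline. For the same reason, a rule that impact counts only when both agree would be a preference, not a necessity.

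**Conclusion.** The concern holds as a conditional one. The protocol's adjustment can leave about (1 − reliability) × gap in the programme estimate, in either direction, and for the IDDS this could be large. The range of 0.13–0.35 SD, with error rates of 13–51% (63 per group) or 20–80% (126 per group), rests on a stable true gap of 0.25–0.5 SD, a one-day reliability of 0.3–0.5 and independent errors. The documents supply none of these. With no gap the error rate stays at 5%, and the bias is smaller if caregivers' reporting errors persist across visits. At reliability 0.95 about 5% of the gap remains.

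A reader might infer that a false programme effect is to be expected. That would go too far: no baseline gap is documented. It can only be said that the design does not exclude one and that the stated adjustment would not fully remove it.

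**What to change.** Keep the baseline-covariate model. Beside it, at least for the IDDS and other outcomes measured with appreciable error, pre-specify the group difference in change from baseline: a group-by-visit contrast with the baseline visit as an outcome, which the GLS model named in the Abstract can accommodate.

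State what each analysis assumes. The change analysis assumes that the groups would have moved in parallel without the programme. The covariate model assumes that they are comparable given the observed baseline. Report both estimates with confidence intervals, and describe an impact as sensitive to the adjustment when they differ materially.

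The cost is a few lines of text and one extra model per outcome, on data already to be collected. The extra analysis is less precise, and some positive findings will be reported more cautiously.

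### The primary outcome, QoL, has no named score or visit, and overall QoL and the QoL constructs are all tested at 0.05, so the chance of a false QoL claim can exceed 5%

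*Protocol article*

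**What the plan says.** Four parts of the protocol article bear on this.

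- **Primary outcome.** "QoL will be measured using Kidscreen health-related QoL questionnaire for children and adolescents". No score (overall or a particular construct) and no visit is singled out.
- **Data management and analysis.** "Multivariate regression analysis will be used for group comparison of overall QoL and the QoL constructs of the intervention and control groups". The section then fixes the level: "All the testing will be done at the 0.05 level of significance". The next-to-last sentence mentions baseline, week 12 and week 24, but in connection with the other outcomes, not QoL.
- **Abstract, Methods.** "Data will be collected at baseline, week 12 and week 24". The abstract also says that a generalised least squares (GLS) regression model will test the study hypotheses.
- **Sample size.** The target is a "difference (d) of 5 points on a 100 point scale of QoL constructs", with 80% power, 1.96 for the two-sided 5% level and a standard deviation of 10. The constructs appear in the plural and none is picked out.

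The article gives no order of testing, no adjustment for multiple tests and no criterion for declaring the programme effective.

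**The concern.** The stated purpose includes testing the efficacy of the programme. Three sections describe the primary endpoint in three ways: as QoL, as QoL constructs, and as overall QoL together with the constructs. The sample size allows for one test at 0.05, while the analysis runs several tests on the primary outcome, each at 0.05.

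With no test named as decisive, the score (and possibly the visit) that supports the efficacy conclusion could be chosen after the data are seen. A reader of the results could not tell whether a significant construct was the planned primary result or the best of several. If the programme had no effect on QoL, the chance that at least one of these tests is significant would be above the 5% that the sample-size section assumes.

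**Working it through.** **1. The plan's own figure.** Inputs from the Sample size section: d = 5, SD = 10, Z for power = 0.84, Z for the two-sided level = 1.96.

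n = 2 × 10² × (0.84 + 1.96)² ÷ 5² = 200 × 7.84 ÷ 25 = 62.72, rounded up to 63 per group.

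This reproduces the stated 63. It is the size for one test at 0.05.

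**2. Number of tests.** With k constructs plus the overall score, there are k + 1 tests per visit. The article does not give k, so k = 2, 5 and 10 are assumptions. One visit gives 3, 6 or 11 tests; two visits give 6, 12 or 22.

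**3. Chance of at least one false positive.** Independence cannot be assumed: an overall score is correlated with its own constructs, and repeat visits measure the same children. The test statistics were therefore simulated under no effect (200,000 draws) as follows.

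- Construct statistics are standard normal with between-construct correlation ρ.
- The overall statistic is the sum of the k construct statistics divided by √(k + k(k − 1)ρ).
- Visits are correlated at τ.
- Each statistic is compared with ±1.96.
- The (ρ, τ) pairs were (0.3, 0.5), (0.5, 0.5), (0.5, 0.7) and (0.7, 0.7), all assumed.

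| Constructs (assumed) | One visit | Both visits |
|---|---|---|
| 2 | 8.7% to 10.4% | 14.0% to 18.5% |
| 5 | 14.9% to 21.3% | 23.6% to 36.0% |
| 10 | 21.2% to 35.2% | 33.0% to 55.5% |

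The lower ends come from the highest correlations. For comparison, overall QoL alone tested at both visits gives 9.0% (τ = 0.5) or 8.4% (τ = 0.7).

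**4. What keeping every test confirmatory would need.** Bonferroni at 0.05/m, with d = 5, SD = 10 and 80% power:

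| Tests m | n per group needed | Power at 63 per group | Power at 126 per group, no loss |
|---|---|---|---|
| 1 | 63 | 80% | 98% |
| 6 | 97 | 57% | 91% |
| 11 | 109 | 49% | 87% |
| 12 | 110 | 48% | 87% |
| 22 | 122 | 40% | 82% |

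The 126 per group in the article is 63 doubled to cover non-response and drop-out, so full power at 126 cannot be counted on.

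**The case against.** Four arguments deserve weight.

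- **Visits.** A reader might infer that QoL is planned to be tested at both week 12 and week 24. The analysis section does not say so. It attaches those visits to the other outcomes, and the abstract says only when data are collected. This stands: testing at both visits is an inference, so the one-visit figures must be given alongside.
- **Joint tests.** A GLS model can give one group effect per outcome across visits, and multivariate regression in its strict sense allows one joint test over the constructs. Either could lower the error rate. This stands as a possibility, but the article does not commit to such a test or say that it must succeed before the separate comparisons are read.
- **Success rule.** A reader might infer that any one significant construct counts as the primary result. The article does not state this. The percentages are rates of false efficacy claims only if that rule is applied. The text does not exclude it, because it gives no success criterion.
- **What an article leaves out.** Testing order and multiplicity are commonly left to an analysis plan. Their absence alone would be no finding. Here, however, the article sets one level for all testing directly after listing several tests of the primary outcome, and its sections differ on what that outcome is.

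A still stronger reading would treat the tests as independent. That gives 1 − 0.95²² = 68% for 22 tests. It cannot apply to an overall score and its own constructs, and it also assumes both visits.

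**Conclusion.** The point holds in this form. The article names QoL as primary without a score or visit, compares the groups on overall QoL and the QoL constructs with every test at 0.05, and sizes the study for one such test. If any single significant QoL result may support efficacy, the chance of a false claim is about 9% to 35% at one visit and about 14% to 55% at both visits.

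These ranges rest on 2 to 10 constructs, an overall score that is the sum of the constructs, correlations of 0.3 to 0.7, and separate tests not preceded by a joint test. At the low end (two highly correlated constructs, one visit) the rate is a little under twice 5%, so the inflation need not be large. The 63 per group is arithmetically correct and is not in dispute.

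**What to change.** In the Primary outcome section and the Data management and analysis section, name one confirmatory test before data collection: overall QoL, intervention versus control, at one stated visit (week 12 or week 24), two-sided 0.05. Say that the 0.05 level for efficacy applies to that test. Report the constructs, the other visit and all other outcomes as secondary or supportive, either as estimates with confidence intervals or with a stated multiplicity adjustment.

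Align the Sample size section with the chosen score. Changing the words alone is not enough. The 5-point difference and the SD are given for the constructs ("of 10 is expected in the QoL constructs between pre and post intervention"), and the overall score may have a different SD. Since n varies with (SD ÷ d)², the investigators need to confirm that both values apply to the overall score or recalculate.

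The cost is small. Construct findings become supportive, and the sample-size assumption must be checked. If d = 5 and SD = 10 are confirmed, 63 per group before inflation remains valid, whereas adjusting over all QoL tests would need about 97 to 122 per group for 6 to 22 tests.
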